**Figure 1 F1:**
[figure not shown]
ESTEEM trial outline and patient flow.

### Inclusion and exclusion criteria

Practices already implementing a documented triage system for handling same-day appointment requests will be excluded. A documented triage system for the purpose of this study is defined as a system involving telephone triage (by a GP or a nurse) to manage more than 75% of all same-day requests. This definition recognises that a great number of GP practices will already undertake some form of telephone triage, and we will document the extent of any such triage in usual care practices as outlined previously. All consecutive patients making telephone requests for same-day consultations will potentially be included. Where an individual patient has multiple same-day consultation requests during the study period, to avoid confusion in following up the contact, only the first of these will be included in the study. We will provide guidance to practices on sampling throughout the working day. Larger practices (> 10,000 patients) may recruit up to 30 patients per day, compared with medium (20) and smaller (< 5,000 patients; 10 to 15) practices. All patients aged < 12 and ≥ 16 years requesting a same-day consultation will be included in respect of the primary outcome measure.

Parents or guardians of children aged < 12 years will be invited to provide consent on behalf of the child. We do not propose to include young people aged 12.0 to 15.9 years in this study, since this will involve receipt of a postal survey along with written consent to review notes to the young person’s address, a process we believe may inadvertently lead to a breach of confidentiality should third parties open or have access to the young person’s mail. Adults > 16.0 years will be included, unless the practice wishes to screen out patients for whom it would be inappropriate to send a questionnaire (for example, patients with recent bereavement, vulnerable adults, et cetera). Reception staff will invite patients making same-day consultation requests to briefly outline the nature of their problem in order to facilitate timely care. Patients seeking urgent care will be excluded from the study if they are (i) too ill to participate
[29] (severe chest or abdominal pain or severe difficulty breathing; vomiting blood; altered consciousness; seizures; pregnancy related problems; or severe psychiatric symptoms); (ii) unable to speak English or (iii) a temporary resident.

### Practice recruitment

A total of 42 practices will be recruited from across four geographical areas (Bristol/Avon, Devon/Cornwall, Norfolk and Warwickshire/West Midlands South). To maximise recruitment we will seek to run the trial through the South West PCRN (Devon Primary Care Trust (PCT) is the host organisation and includes areas to Gloucester/Bristol and Central England PCRN (West Midlands South). Two of the four centres link directly to the South West PCRN, each centre having close links with the coordinating hub hosted in the University of Exeter Medical School. We will employ a two-stage approach to the recruitment of practices: (1) a written letter inviting participation to all practices in the four geographical areas, co-signed by the trial Principal Investigator, the local co-applicant, and the local National Institute for Health Research (NIHR) PCRN clinical lead and (2) recruitment workshops for those practices indicating an interest in participation, where the trial design and methods will be explained and provide an opportunity for practices to clarify their questions.

We are not complacent regarding the challenges of practice recruitment, recognising high-level evidence on the challenges of recruitment to large scale clinical trials of complex interventions
[34]. Building on the experience of a previous limited survey, during the pilot phase we undertook a further survey of practices seeking expressions of interest in participation. We will provide a carefully presented recruitment pack to practices expressing preliminary interest; we anticipate doing this during personal briefing meetings (for which the practice would be remunerated) rather than as mailed material. We anticipate writing to 600 practices with a project outline, meeting with 125 (20%) practices that have expressed interest in the study in screening meetings (either jointly or individually), and securing participation from around one-third of these (42 practices). The PCRN in the South West, Central (West Midlands South) and East of England covers approximately 1,500 practices. We will prioritise practices in workable proximity to recruitment centres (taking account of relevant sampling issues). Regarding generalisability, it is recognised that only practices willing to participate can be included in the trial. Although some practices may not wish to participate in a complex RCT where they have no choice about which arm they would be allocated to, it may be that many would be prepared to instigate a triage system that had been shown to work in a high quality study.

### Randomisation

Individual patient-level randomisation is not practical, does not reflect the practice-wide reality of triage system implementation and is vulnerable to contamination. Instead we will use a cluster RCT design
[35]. Patients in the usual care group may be influenced by system-level changes such as the changed availability of different types of appointments and changes to the process of care. Randomisation will be carried out by an independent statistician at the Peninsula Clinical Trials Unit and codes held remotely. The sequence of randomisation will be computer-generated and stratified for geographical location, practice deprivation and practice list size. Stratification by locality will ensure that we have a similar number of standard care/GP/nurse triage practices in each geographical area. Simple randomisation will be used for the first twelve practices and then minimisation applied to ensure balance of stratification variables across the three arms.

### Outcome measures

The terms, telephone consultation, and triage, have often been used interchangeably in research reports
[26]. Whilst triage is a concept drawing on ideas of prioritising and rationalising workload, we have already referred to the uncertainty in the academic literature of the relationship between triage and the assessment/management of patients. Triage concerns prioritising the use of resources and determining the necessary speed of response. Telephone consultations may also have other benefits in terms of easier access to care for patients. Our study will therefore incorporate these important outcomes: (1) total primary care workload (primary outcome measure, including primary care, GP out-of-hours, A&E and walk-in centre attendance); (2) NHS resource use/cost and non-attendance rates in primary care and (3) patient experience of care, patient safety, and patient health status.

### Primary outcome

The primary outcome measure is the number of healthcare contacts taking place in the four-week period following the index same-day consultation request. The number of contacts will include the initial clinical assessment contact, and will thus include the triage contact in the two intervention conditions. The total number of contacts per 1,000 patients requesting same-day consultations in each of the trial conditions will be derived from numbers of GP, practice nurse, GP out-of-hours, A&E, and (although they may not impact significantly on GP workload
[36]) NHS WIC attendances. Data collection, capturing information on timing (am/pm), and type (face-to-face, telephone, home visit, GP out-of-hours, A&E and WIC attendance) of primary care contacts in all trial practices will take place as part of a note review occurring at least twelve weeks after the index consultation request with data extracted from the primary care medical record. We will count the day of the index request as day 1 (same day), and include the following 28-day period (day 1 to day 28 inclusive) starting from the day following the consultation request.

### Secondary outcomes

1.Descriptive study of patient flow: we will describe the management and interim and final disposition of patients in the working day in which they request a same-day consultation, up to the point of final contact within that working day, for each of the trial conditions.

2.Primary care NHS resource use: we will capture NHS primary care resource use by collecting data on the number of contacts resulting for patients in the three trial conditions, as for primary outcome, over a four-week follow-up. We will collect actual consultation length for initial triage and usual care (face-to-face or telephone) consultations (described below). We will estimate the length of subsequent consultations, for same-day and four-week follow-up periods based on the recorded start and end times of a sample of consultations captured over two randomly selected days in each practice during the patient recruitment period. For costs, see health economic evaluation below. Non-attendance rates for allocated appointments in the month following the same-day request will be described and compared between trial conditions using data extracted at practice record review.

3.Patient experience of care, safety, and health status: these patient-reported outcomes will be collected by postal questionnaire four weeks following the request for a same-day consultation. This time frame has been selected to capture a period for optimal recall, which may encompass events and experiences that could feasibly be linked to the initial reason for contacting the GP practice for a same-day consultation.

For patient experience of care, whilst this study focuses on patients’ experiences of an episode of care delivered following a same-day consultation request, and possibly involving multiple healthcare contacts during the course of the index day, currently available survey instruments suitable for use in a UK setting have focused on the evaluation of individual consultations
[37,38] or aggregate (practice-based) care. No validated instruments for assessing the patient’s experience of an overall episode of care following such a request, and possibly involving multiple interactions, have been identified. We propose to use a modification of the new national GP patient survey instrument for the purposes of monitoring patient experiences of care in this study. This study team is in a unique position
[39,40] to have early access to this instrument for research purposes.

We will survey patients who have requested same-day consultations in each of the three trial conditions using a modified version of the national survey instrument. Whilst the national survey explores patients’ experiences of care in the past 6 months, we will modify relevant questions to focus on the participants’ recent experiences of care following their same-day consultation request.

The responsiveness of the consultation management system will be assessed using patient reports of care received (for example, how quickly care was provided and overall satisfaction) and their evaluations (using a 5-point Likert scale)
[41,42] of the timeliness and convenience of the response
[43] to the original same-day consultation request incorporated into the follow-up questionnaire.

For patient safety, deaths within 7 days of the same-day consultation request (from practice records), and attendance at A&E within four weeks and number and length of stay of emergency (unplanned, that is, admission with no evidence of prior planning of that admission within a one-day period at notes review) hospital admissions within 7 days of the index consultation (from primary care records examined twelve weeks after the same-day consultation request).

Patient health status will be assessed by the widely used EuroQol Group 5-Dimension Self-Report Questionnaire (EQ-5D) measure
[44] incorporated into the follow-up questionnaire, along with a question on problem resolution
[27,28] (5-point Likert scale).

For descriptive data, we will collect patient-level (for example, on age and gender) and practice-level (for example, on practice size, staffing and deprivation index) data. Two approaches to defining patient casemix will be adopted: (i) we will record morbidity on the basis of the principal systems involved (after
[28,29]), allowing for clinicians to record up to three systems in respect of each consultation; (ii) an 8-point score will be used to define the complexity of the case (after Howie
[45]) with each consultation being defined as having substantial (2 points), attributable (1 point) or no content (0 points) in respect of each of four domains, namely, physical, social, psychological or other (for example, administrative) components to the consultation.

Timely care will be assessed as (i) proportion of participants receiving initial advice in any form from the practice (that is, not including out-of-hours care, WIC or A&E attendance) the same day (that is, within routine surgery opening hours) following a same-day appointment request and (ii) delay (days) to final episode of care in the week following the index consultation request. Definitive first pass management will be assessed as the number of consultations (including index triage consultation) in the week following the index consultation request; patient reports of problem resolution and patient-reported experience of care.

Efficient management of consulting time will be assessed by examination of the extent to which additional consultations introduced as a result of GP or nurse triage are offset by altered patterns of subsequent consultations by the patient in (i) the same day as the request; (ii) the week following the request and (iii) the 28 days (four weeks) following the request; we will count the day of the index request as day 1 (same day), and in respect of (ii) and (iii) include the following 7-day period (day 1 to day 7 inclusive) or 28-day period (day 1 to day 28 inclusive) within these defined time periods.

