### Primary care workload

In the short term, telephone triage, whether by doctor or nurse, appears to reduce GP workload by around 40%
[3,12], but may be associated with an increase in later return consultations of a roughly similar magnitude (30%
[3], 50%
[13]), in effect smoothing out the peaks and troughs of GP workload associated with same-day appointment requests but raising concerns regarding patient safety, convenience and cost-effectiveness.

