### Patient safety

Telephone consultation appears safe and effective
[18,19] although one Swedish study
[20] noted that nurses often used self-care advice and over-rode software-determined recommendations on management. A recent Dutch study highlighted concerns regarding information gathering in telephone triage when delivered without interactive computerised decision support, relying only on clinical protocols
[21]. Studies
[8,20,22,23] have highlighted the importance of training in the use of decision support software in addressing patient safety issues. Nurse telephone triage using national guidelines (but not with interactive computer-based decision support) was judged to be efficient, although some concerns have been raised in respect of patient safety
[24]. One study
[3], adopting a triage system involving computerised management protocols developed by the practice, identified a 30% increase in the number of return consultations within the nurse telephone triage group, and although actual numbers were small, a substantial increase (200%) in Accident and Emergency (A&E) attendance. Although computerised, such a system did not provide interactive decision support ([name]; personal communication) such as is now available within a number of NHS primary care computer systems and which we propose to examine in this study
[25]. The other trial by Richards *et al*.
[14] used computerised decision support algorithms for NHS Direct triage nurses, but not for nurses acting in primary care. A systematic review
[26] of nine studies of telephone consultation and triage identified the possibility that telephone management may lead to a delay in providing definitive care.

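### The outcome for delay to final care ignores contacts after day 7, so a return deferred past one week scores as a shorter delay; deaths and unplanned admissions also stop at day 7

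*Protocol article*

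**What the plan says.** All references are to the protocol article.

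- **Timely care (Secondary outcomes).** There are two measures. The first is the proportion of patients given initial advice by the practice on the same day. The second is "delay (days) to final episode of care in the week following the index consultation request".
- **First-pass management (Secondary outcomes).** This uses the "number of consultations (including index triage consultation) in the week following the index consultation request", together with patient-reported problem resolution and experience.
- **Patient safety (Secondary outcomes).** A single sentence sets three windows: deaths within 7 days of the request; "attendance at A&E within four weeks"; and number and length of stay of emergency "hospital admissions within 7 days of the index consultation".
- **Primary outcome.** Contacts with GP, practice nurse, out-of-hours service, A&E and walk-in centre are counted over 28 days. The rule is to "include the following 28-day period (day 1 to day 28 inclusive) starting from the day following the consultation request". Data come from a notes review at 12 weeks or later.
- **Background.** Under Primary care workload, triage appears to cut GP workload in the short term "but may be associated with an increase in later return consultations of a roughly similar magnitude" (30% and 50% in two studies). Under Patient safety, a systematic review "identified the possibility that telephone management may lead to a delay in providing definitive care".

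**The concern.** A delay measure should rise as care is completed later. This one stops looking at day 7, so it rises with the day of the last contact only up to that point. A return pushed beyond it no longer counts, and the score falls. The background names later returns and delayed definitive care as open questions about triage, and this is the outcome a reader would consult on the second of them.

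The other timely-care measure does not compensate. It asks whether some advice was given on the same day, which a call-back system is built to deliver. A favourable result on both measures could therefore be reported as more timely care even if episodes were finishing later.

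The safety windows raise a smaller, related point. An A&E attendance on day 10 is a safety event. An unplanned admission arising from it, or a death that day, is not in any listed safety outcome.

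**Working it through.** **1. Windows side by side**

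| Outcome | Window |
|---|---|
| Same-day initial advice | day 1 |
| Delay to final episode of care | 7 days |
| Consultations, for first-pass management | 7 days |
| Deaths | 7 days |
| Unplanned admissions, number and length of stay | 7 days |
| A&E attendance (safety) | 4 weeks |
| Contacts (primary outcome) | 28 days |
| Contact patterns, for efficient use of consulting time | same day, 7 and 28 days |
| Problem resolution, EQ-5D, experience | asked at 4 weeks |

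**2. Ranking of individual patients.** Take the index day as day 1 and delay as day of last counted contact minus 1. Each patient has an index contact on day 1.

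- Patient A returns on day 6: 7-day score 6 − 1 = 5; 28-day score 5.
- Patient B returns on day 9: 7-day score 1 − 1 = 0; 28-day score 9 − 1 = 8.
- Patient C never returns: 0 on both.

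The 7-day score puts B ahead of A although B's care ended later. The article gives no scoring rule for a patient with no further contact, so B's 0 is the natural reading and not a stated one. One conclusion does not depend on that rule: B and C have identical records through day 7, so no rule using only the first week can separate them. Counting seven days from the day after the request would move the boundary by one day, and day 9 would still fall outside.

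**3. Effect on arm means (illustration, all inputs assumed).** The document gives no return rates by day. Let *r* be the share of patients with one return, *e* the share of usual-care returns falling in days 2–7, and *s* the share of those that triage moves to days 8–28. With even spread, early returns have mean delay 3.5 days (mean of 1 to 6) and late returns 17 days (mean of 7 to 27).

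- 7-day mean: usual care 3.5·*r*·*e*; triage 3.5·*r*·*e*·(1 − *s*).
- 28-day mean: usual care *r*[3.5*e* + 17(1 − *e*)]; triage *r*[3.5*e*(1 − *s*) + 17(1 − *e*(1 − *s*))].

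For *r* = 0.30, *e* = 0.50, *s* = 0.50:

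- 7-day: usual care 0.30 × 0.50 × 3.5 = 0.53; triage 0.26. Triage looks faster.
- 28-day: usual care 0.30 × (1.75 + 8.5) = 3.07; triage 0.30 × (0.875 + 12.75) = 4.09. Triage is slower.

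Over *r* = 0.20–0.40, *e* = 0.30–0.70 and *s* = 0.25–0.50, the direction reverses in every combination. The 7-day means run 0.10–0.73 (triage) against 0.21–0.98 (usual care). The 28-day means run 1.98–5.99 against 1.51–5.18.

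The reversal is built into the assumption. Any *s* above 0 lowers the 7-day triage mean by 3.5·*r*·*e*·*s* and raises the 28-day mean by 13.5·*r*·*e*·*s*. If triage instead added returns inside days 2–7, both measures would show triage as slower.

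**4. Sample size.** The stated figures concern the 28-day primary outcome only, and they reproduce. With SD √[(0.78² + 1.79²)/2] = 1.38 and difference 0.36, 90% power needs 310 per group against 305 stated. Then 305 × 12.3 ≈ 3,751, and 3,751/(0.94 × 0.90 × 0.70 × 0.90) ≈ 7,038 against 7,046 stated. Nothing here changes them.

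**The case against.** A reader might infer that any return or harm after one week is recorded as timely and safe. The document does not support that. Every listed contact to day 28 counts in the primary outcome. The comparison of contact patterns at the same day, 7 days and 28 days would show extra late contacts. A&E attendance runs to four weeks, and problem resolution and EQ-5D are asked at four weeks. This objection stands and sets the limits of the point: late returns are seen as volume but not as delay, and late harm is seen only through A&E attendance and patient report. The questionnaire cover is partial. The expected response is 70%, the article treats its EQ-5D analysis as exploratory because there is no baseline, and a questionnaire cannot record deaths.

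A reader might also infer that the delay outcome is biased towards triage. That needs returns to move from within the first week to after it. The background speaks of later returns but gives no day, so the shift is possible, not shown.

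A third tempting reading is that 28-day windows would hold two to four times as many deaths or admissions. No event rates are given, so that cannot be derived. Nor is the share of follow-up after day 7 (21/28 = 75%) a measure of bias.

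The short window can be defended. These are same-day requests, and a last contact by day 28 takes in unrelated care that dilutes a real difference. That is a good reason not to replace the 7-day definition. It is a weaker reason for having no 28-day figure, because the article supports its four-week questionnaire partly on the ground that events over that period may plausibly stem from the original request.

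Different windows for different safety events are not a contradiction. A&E attendance also belongs to the 28-day primary outcome, which may explain its longer window. Deaths and admissions are listed as safety outcomes, not as measures of delay. Finally, a full analysis plan exists and is not shown. It may state the scoring rule, but a rule confined to the first week cannot recover what happens after it.

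**Conclusion.** The point holds as a weakness in secondary outcomes. As worded, the delay outcome can rank a return deferred past day 7 as shorter delay than a return within the week. That follows from the definition, given only that a patient with no further contact in the week scores zero. Whether it favours triage depends on triage displacing returns past day 7, which is plausible from the background but not established. The illustration shows that the direction can reverse, not that it will, and the size of any bias cannot be derived from the document.

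Separately, deaths and unplanned admissions on days 8 to 28 enter no listed safety outcome, while A&E attendance over the same days does, and no reason is given. This is a gap in coverage, not an error.

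The primary outcome, its analysis and the sample size are unaffected.

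**What to change.** Keep the 7-day outcomes as they are. Add the following as pre-specified supporting analyses:

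1. Delay to final contact over days 1 to 28, from the contacts already extracted for the primary outcome, with the score for a patient who has no further contact stated.
2. Deaths within 28 days.
3. Unplanned admissions within 28 days, number and length of stay, under the existing definition of unplanned.

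State that a shorter 7-day delay will not be interpreted as more timely care unless the 28-day measure agrees.

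The cost is small. The notes are read at 12 weeks or later, and the Case note review section already lists hospital admissions among the items recorded. The work is a wording change and a longer look-back for deaths and admissions. The downside is that the 28-day versions take in more unrelated events, which dilutes differences between arms. Reporting them beside the 7-day figures keeps that visible.

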### Feasibility

Previous studies suggest that around 50% of nurse triage calls may be handled by telephone advice alone
[5-8]. However, such studies have been small or focused on out-of-hours care. Use of telephones (fixed or mobile) is now virtually universal in Britain
[9], and recent years have seen a near quadrupling in the proportion of GP consultations conducted on the telephone, from 3% (1995) to 11% (2007)
[10,11].

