### Outcome measures

The identification and choice of the most relevant outcomes has been a contentious issue in previous evaluations of triage systems in primary care
[26]. Most studies to date have assessed primary care and hospital service use and workload. However, these outcomes may not in themselves capture the aim of triage services, and more broadly, the aim of primary care. In the context of patients presenting requests to be seen on the same day, we propose that the purpose of a primary care consultation management system is to provide an administrative framework for practices (i) to facilitate the safe, timely, and definitive (first pass) management of such patients and (ii) to facilitate the timely and efficient management of primary care consulting time resource. Our proposed outcome measures (below) reflect that understanding. Additionally, it may well be that a large-scale study to inform the optimal management of same-day requests will ultimately benefit other providers (for example, out-of-hours GP service of NHS 24 Direct) that may steer patients towards general practice for semi-urgent problems.

UK-based trials of primary care telephone consultation and triage
[3,5,12,13] have been conducted in relatively small populations and/or in limited numbers of practice settings, and without the use of computerised interactive decision support. Despite uncertainty about the benefits and costs, many practices operate GP- or nurse-led triage systems of different types as a way of providing fast access to care for patients and in order to manage practice workload. The NHS Institute for Innovation and Improvement has recently promoted a new model of GP-led telephone triage
[30], the Stour access system, but without any robust evidence about benefits. We therefore propose to address this important agenda for both UK and international primary care in a large-scale experimental study of two forms of triage currently being promoted by the NHS for use in UK Primary Care. Our findings may be generalisable to other health settings, especially those with strong primary care-based health care systems.

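### The record-based measure of definitive first-pass management counts a same-day visit booked at triage and a later return for an unresolved problem as the same thing

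*Protocol article*

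**What the plan says.** The Background (Outcome measures) names two purposes of a consultation management system. The first is "to facilitate the safe, timely, and definitive (first pass) management of such patients".

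Secondary outcomes turns this into a measurement rule: "Definitive first pass management will be assessed as the number of consultations (including index triage consultation) in the week" after the index request. The same sentence adds two further measures, "patient reports of problem resolution and patient-reported experience of care". The next paragraph of that section makes the index day day 1 and describes the week as "day 1 to day 7 inclusive".

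For the primary outcome, the counting rule covers the first contact in every arm: "The number of contacts will include the initial clinical assessment contact, and will thus include the triage contact in the two intervention conditions".

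A separate item, efficient management of consulting time, looks at "the extent to which additional consultations introduced as a result of GP or nurse triage are offset by altered patterns of subsequent consultations". It does so for the same day, the week and 28 days, each window starting on day 1.

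**The concern.** In a triage arm, a patient who needs to be seen has a call and then a visit. If both fall on the index day and nothing follows, the count is 2. A usual-care patient who is seen on day 1, is not helped and comes back on day 4 also scores 2. One request was settled on the day and the other was not, yet the measure treats them alike.

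The Background (Primary care workload; Patient safety) raises a possible rise in return consultations after triage. The seven-day total mixes that signal with the triage step itself. A real fall or rise in returns could be masked by the number of calls that lead to a visit, and a higher score in a triage arm could be read as less definitive care when it reflects only the extra step.

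**Working it through.** The protocol states no expected value for this measure, so there is no figure to reproduce. The check works out what the written rule yields when nobody returns.

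**Inputs**
- Share of calls closed by telephone, nurse triage: the Background (Feasibility) says that "around 50% of nurse triage calls may be handled by telephone advice alone", so p = 0.50.
- Share closed by telephone, GP triage: one-third, the figure claimed for the Stour system (GP-led telephone triage), so p = 0.33.
- Further contacts per usual-care patient in the week, r: not given. Range shown: 0 to 0.7.

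**Assumptions**
- The primary-outcome rule on the first contact, and the day 1 to 7 window, apply to this count.
- A call not closed by telephone leads to exactly one further contact, on the index day.

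**Formulas**
- Triage arm with no return after the index day: 1 + (1 − p).
- Usual care without triage: 1 + r.
- Difference: (1 − p) − r.

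**Results with no returns in the triage arm**
- Nurse triage: 1 + 0.50 = 1.50.
- GP triage: 1 + 0.67 = 1.67.

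| r in usual care | Usual-care score | Nurse minus usual care | GP minus usual care |
|---|---|---|---|
| 0 | 1.00 | +0.50 | +0.67 |
| 0.2 | 1.20 | +0.30 | +0.47 |
| 0.4 | 1.40 | +0.10 | +0.27 |
| 0.5 | 1.50 | 0.00 | +0.17 |
| 0.7 | 1.70 | −0.20 | −0.03 |

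The scores tie at r = 0.50 (nurse) and r = 0.67 (GP). At the extremes, if every call is closed by telephone (p = 1) the difference is −r, so triage ties or scores better. If every call is converted (p = 0) it is 1 − r.

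**Usual care that already triages.** Practices are excluded only if they triage more than 75% of same-day requests (Inclusion and exclusion criteria). If usual care triages a share u and half of those calls convert (assumed), it scores 1 + 0.5u + r. With r = 0:
- u = 0.50: usual care 1.25; gap 0.25 (nurse) and 0.42 (GP).
- u = 0.75: usual care 1.375; gap 0.125 (nurse) and 0.29 (GP).

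**Size of the signal of interest.** The Background cites a 30% rise in return consultations. As an absolute change this is 0.3 × r: 0.03 at r = 0.1 and 0.21 at r = 0.7. Against usual care that does not triage, the built-in step of 0.50 to 0.67 exceeds it across this range.

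**Cross-check.** The four-week planning means are 1.02 (usual care) and 1.38 (nurse triage). If they counted one first contact for every patient, further contacts were 0.02 and 0.38, which would put the converted share at no more than 0.38, below the 0.50 used above. The protocol does not say how that trial counted the first contact, so this shows only that 1.50 is an illustration and not a forecast.

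**The case against.** A reader might infer that a triage arm in which nobody returns must score worse than usual care by design. The document does not support that. A call closed by telephone scores 1, the same as a usual-care patient seen once, and only converted calls score 2. The arm-level difference depends on the converted share, on r and on how much triage usual care already does.

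A reader might also infer that the whole outcome is biased against triage. It is not: problem resolution and patient experience belong to the same construct and do not depend on contact counts. They do come from a postal survey with an expected 70% response (Feasibility, under Methods/design), so they do not repair the record-based part.

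The strongest defence is conceptual. If the triage call is itself the first pass, a call that needs a second contact did not settle the request, and counting it is coherent. But the protocol never says this. It makes definitive management an aim of the system, makes the GP's booking of the visit part of the intervention, and, when discussing patient experience, describes an episode that may involve several contacts on the index day.

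It is also fair that the protocol qualifies both closure shares: the nurse studies were small or out-of-hours, and the Stour claim lacks other published support. The overlapping windows do not prevent the offset from being estimated, since mean differences for days 2–7 and 8–28 follow by subtraction.

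Finally, a days 2–7 count used alone has faults of its own. It would call a same-day repeat contact or A&E visit definitive, and would penalise a patient first seen on day 2. This is why it should be added and not substituted.

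**Conclusion.** The point holds for one component of one secondary outcome. The rule is explicit, so this is not a detail left to the analysis plan, and the component cannot separate planned same-day visits after triage from true returns. With no returns after the index day, the triage arms score about 1.50 and 1.67 against 1 + r in usual care, so the difference ranges from +0.50 and +0.67 at r = 0 to nil at r = 0.50 and 0.67. It is smaller where usual care already triages.

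These sizes rest on the qualified closure shares, one same-day visit per converted call, and the primary-outcome counting rule carrying over. The failure to separate the two kinds of contact does not depend on them; it needs only that some calls lead to a visit. The change is worth making because definitive management is a stated purpose of the system and the remedy is nearly free.

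**What to change.** - Keep the seven-day total, triage call included, and label it a workload count.
- Add, as the record-based measure of definitive management, the number of consultations after the index day (days 2–7) and the proportion of patients with none. Define both identically in all arms and analyse them in the planned random-effects framework, with the family and link suited to a count and to a proportion.
- Report separately same-day repeat or A&E contacts, and patients whose first contact came after day 1, so that neither group is misclassified.
- Show the offset for day 1, days 2–7 and days 8–28 beside the cumulative windows.
- Leave the problem-resolution and experience items as they are.

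The cost is wording in the protocol and analysis plan, and one or two more derived variables. No new data are needed, because the same-day, 7-day and 28-day windows already require contacts to be dated at note review. No clinical procedure changes.
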